**Reference standard HMOD assessment**

In the heart, left ventricular systolic dysfunction will be assessed with a transthoracic echocardiogram (TTE), and left ventricular hypertrophy will be assessed with a TTE and 12-lead electrocardiogram (ECG). In the eye, hypertensive retinopathy will be assessed from retinal images captured by a fixed retinal camera and graded for hypertensive retinopathy by trained staff. Kidney dysfunction will be assessed using clinical laboratory assessment of blood and urine to measure serum creatinine levels and estimate glomerular filtration rate (eGFR) and glomerular function using urine albumin:creatinine ratio and proteinuria. Finally, we will assess pulse wave velocity and arterial stiffness using a specialised blood pressure cuff (Arteriograph, TensioMed, Hungary).

**Point-of-care HMOD assessment**

Point-of-care assessment of left ventricular systolic dysfunction and left ventricular hypertrophy will be assessed using a mobile phone based 6-lead ECG (KardiaMobile, AliveCor, United States of America) coupled with artificial intelligence (AI) tools developed for ECG analysis
^
48
^. In the eye, we will assess hypertensive retinopathy using a handheld, mobile phone based, non-mydriatic retinal camera (Remidio, India). Retinal image grading will be conducted by the same staff who graded the reference standard images. Finally, kidney dysfunction (defined as serum creatine levels, eGFR and glomerular function) will be measured using urine dipsticks, and POC clinical chemistry devices (Abbott iStat, Abbott, United States).

**
*Genetic sampling*.** For the genetic analyses, DNA will be extracted from whole blood samples using Qiagen DNA Blood Mini kit. DNA extraction will make use of blood samples drawn for HMOD measurement and no new blood sample is required. We will then use PCR to determine presence of the genotypes of interest, including malaria and trypanosomiasis protective polymorphisms (Dantu, SCT, APOL1 or APOL2)
^
36,
37
^. These analyses will be conducted in KWTRP.

**
*Health economics assessment*.** We will use the human capital approach to collect primary data on patient costs including the opportunity cost of time spent administering blood pressure-monitoring methods, missing productive activity and any out-of-pocket costs incurred for undergoing study procedures. Health system cost data will be collected using a micro-costing, ingredient-based approach. Data will be collected from a structured questionnaires administered to three CHWs from each study site, structured observations of CHW and user time spent on BP and HMOD measurement, and a survey using a structured questionnaire to 200 individuals diagnosed with hypertension
^
49
^.

### Statistical analysis plans

A detailed statistical analysis plan will be produced before data collection is completed and uploaded to a public repository. A summary of statistical analysis approaches that will be taken for this study is outlined here.

**
*Hypertension prevalence*.** We will estimate sensitivity; specificity; positive and negative predictive values; and the positive and negative likelihood ratios of each BP measurement approach compared to the reference standard 24-hour BP measurement method.

**
*Identifying hypertension risk factors*.** The primary outcome will be hypertension, defined as a BP of >140/90mmHG using 24-hour BP measurement, or ongoing therapy with anti-hypertensives. We will determine the relationship between the candidate risk factors and blood pressure and hypertension using multivariate linear and logistic regression methods as appropriate. We will include confounders in the regression models based on results of univariate models and existing literature on the subject.

**
*Prevalence of organ damage*.** We will analyse the overall prevalence of HMOD and report age- and sex-standardised and stratified prevalence rates. We will also analyse prevalence rates stratified by type of HMOD (left ventricular hypertrophy, impaired left ventricular systolic function, renal dysfunction, hypertensive retinopathy, or arterial stiffness). Finally, we will construct logistic regression models to identify the participant parameters associated with presence of HMOD.

**
*Accuracy of POC diagnostic tools*.** The diagnostic accuracy of the POC assessments will be estimated using sensitivity; specificity; positive and negative predictive values; and positive and negative likelihood ratios of each POC parameter compared to the conventional measurement. These comparisons will be:

1) Left ventricular systolic function: Smartphone-based ECG (analysed with Mayo Clinic trained AI algorithms) compared to transthoracic echocardiogram (reference standard).2) Left ventricular hypertrophy: Smartphone-based ECG (analysed with validated and trained AI algorithms) compared to 12-lead ECG and transthoracic echocardiogram (reference standard).3) Hypertensive retinopathy: Smartphone-based retinal imaging compared to clinical grade retinal camera (reference standard) in detecting HMOD.4) Renal dysfunction: POC clinical chemistry and urinalysis dipstick compared to conventional clinical laboratory assessment of blood and urine markers for renal function

**
*Cost effectiveness analysis*.** We will model the comparative cost-effectiveness of different decision-making approaches for initiating treatment of hypertension. We will define cost-effectiveness by comparing the costs (to be obtained from primary data collection) and outcomes (to be obtained from secondary sources) of implementing the four different BP measurement approaches, as well as the reference and PoC assessments of HMOD, to guide initiation of treatment. This analysis will be used in developing the community-centred programme at a later stage of the project.

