### Study aim and objectives

We aim to improve the evidence base for diagnosis and risk estimation for a CHW-led community-centred hypertension programme in two rural communities in SSA.

We have the following specific objectives:

1. To determine the accuracy of three alternative blood pressure measurement methods relative to the reference standard and establish the prevalence of hypertension2. To determine the relationship between systolic blood pressure and potential risk factors3. To determine the prevalence of HMOD4. To determine the accuracy of innovative POC technologies to identify patients with HMOD5. To estimate the likely cost-effectiveness of different combinations of blood pressure and HMOD measurements to initiate pharmacological treatment in people with hypertension

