### Sample size

The overall sample size for the study is based on the assessment of hypertension prevalence. Assuming a prevalence of hypertension of 25–35%, as detected by the reference standard method (24-hr-ABPM), we will require 832–1003 participants to generate validity parameters for hypertension prevalence with a precision of ±3% overall and ±5% at each of the two sites
^
24,
41
^. We have made a provision for loss of data in 25% of participants due to poor data quality, taking the total number of participants required to 1250, equally divided between Kilifi (N=625) and Kiang West (N=625). This overall sample size will provide sufficient statistical power to address the other aims stated above.

In our assessment of BP and risk factors, and assuming for illustrative purposes that 10% of individuals will have any of the putative factors and that the standard deviation of systolic blood pressure will be 15 mmHg, then 1,003 participants will provide at least 80% statistical power for an alpha of 0.05 to detect a 4mm Hg difference in systolic BP in those with and without the exposure of interest.

Assuming a prevalence of hypertension detected by the reference standard method (24-hr-ABPM) of 30%, we estimate that approximately 300 participants from those recruited in Objective 1 will be classified as hypertensive. With 300 hypertensive patients, we would be able to estimate the confidence interval for a conservative HMOD prevalence of 35% with lower and upper intervals of 29.7% and 40.4% respectively, and that we will have over 95% power for an alpha of 0·05 to test the null hypothesis that the prevalence of HMOD is below 25%. To further explore the difference in the prevalence of HMOD in the hypertensive and general population, we intend to assess all participants recruited into the study for HMOD.

When measured with the reference standard techniques, we expect a 35% prevalence of HMOD among the 300 estimated hypertensive participants and approximately 5% prevalence in the remaining non-hypertensive participants. This will provide us with a total available sample of 153 participants with HMOD. Assuming at least 85% sensitivity of detection of HMOD by the POC strategies we will have at least 80% power for an alpha of 0.05 to test the null hypothesis that the sensitivity is below 75%. As above, we will conduct POC HMOD assessments on all participants.

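### Objective 2 and its power statement concern continuous systolic BP, but the analysis section labels binary hypertension the primary outcome and gives no power for it

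*Protocol article*

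**What the plan says.** - Study aim and objectives, Objective 2: "To determine the relationship between systolic blood pressure and potential risk factors". The abstract describes this objective in the same terms.
- Sample size: 1,003 participants are said to give at least 80% power at an alpha of 0.05 "to detect a 4mm Hg difference in systolic BP in those with and without the exposure of interest". The inputs are "assuming for illustrative purposes that 10% of individuals will have any of the putative factors" and "the standard deviation of systolic blood pressure will be 15 mmHg". The section also says that the overall sample size gives enough power for the other aims.
- Statistical analysis plans, paragraph on identifying hypertension risk factors: "The primary outcome will be hypertension". With its definition, the sentence reads "The primary outcome will be hypertension, defined as a BP of >140/90mmHG using 24-hour BP measurement, or ongoing therapy with anti-hypertensives".
- The next sentence of that paragraph plans to estimate the "relationship between the candidate risk factors and blood pressure and hypertension using multivariate linear and logistic regression methods as appropriate".
- The paragraph ends with a rule for adjustment: "We will include confounders in the regression models based on results of univariate models and existing literature on the subject".

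**The concern.** The outcome called primary for the risk-factor analysis is neither the outcome in the objective nor the one in the power statement. The two outcomes can give different answers for the same exposure, and the text does not rank them beyond that label. As published, the protocol would support presenting either one as the main result once the data are known. Dichotomising a continuous measurement also costs power, and the article does not say how much remains.

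The adjustment rule is a second, smaller point. It lets univariate results help to decide which confounders enter. A variable can look unrelated to the outcome on its own and still confound once other variables are in the model, so screening can drop it. Confidence intervals from the final model then ignore the selection step.

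**Working it through.** **Inputs from the Sample size section:** difference 4 mmHg, SD 15 mmHg, 10% exposed, N=1,003 (100.3 exposed, 902.7 unexposed), alpha 0.05 with sidedness not stated, hypertension prevalence 25–35% (30% used for Objective 3), 1,250 recruited.

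**Step 1. Reproduce the stated power for systolic BP.** Power = Φ(4/SE − z), with SE = 15 × √(1/100.3 + 1/902.7) = 1.579, so 4/SE = 2.534.

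- Two-sided (z = 1.960): Φ(0.574) = 71.7%.
- One-sided (z = 1.645): Φ(0.889) = 81.3%.
- N=1,250, two-sided: SE = 1.414, 4/SE = 2.828, Φ(0.868) = 80.7%.

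The stated figure of at least 80% is therefore recovered at N=1,003 only with a one-sided test, or with a two-sided test if all 1,250 give usable data.

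**Step 2. Translate 4 mmHg into hypertension.** Assume normal systolic BP with equal SD and a systolic cut-off c (in SD units) that gives 30% prevalence overall:

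0.9 × P(Z > c) + 0.1 × P(Z > c − 4/15) = 0.30, so c = 0.553.

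This gives p0 = 29.0% in the unexposed and p1 = 38.7% in the exposed, a difference of 0.0972 and an odds ratio of 1.55.

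**Step 3. Power for the binary outcome.** Power = Φ((0.0972 − z × SE0)/SE1), where

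- SE0 = √(0.30 × 0.70 × (1/100.3 + 1/902.7)) = 0.0482
- SE1 = √(0.387 × 0.613/100.3 + 0.290 × 0.710/902.7) = 0.0509

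Two-sided: Φ(0.052) = 52.1%. One-sided: Φ(0.351) = 63.7%. At N=1,250 two-sided, SE0 = 0.0432 and SE1 = 0.0456, giving Φ(0.274) = 60.8%.

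| Setting | Systolic BP | Hypertension | Loss (points) |
|---|---|---|---|
| N=1,003, two-sided | 71.7% | 52.1% | 19.6 |
| N=1,003, one-sided | 81.3% | 63.7% | 17.6 |
| N=1,250, two-sided | 80.7% | 60.8% | 19.9 |
| N=938 (1,250 less 25%), two-sided | 68.8% | 49.6% | 19.2 |

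Over 25–35% prevalence, binary power in the first three rows is 51–53%, 62–65% and 59–62%, so the loss runs from about 17 to 22 points.

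**Step 4. Detectable effect for hypertension.** At N=1,003 two-sided, 80% power needs p1 of about 42.9% against p0 of 29.0%. The odds ratio is (0.429/0.571)/(0.290/0.710) = 1.83 to 1.84, depending on rounding, which corresponds to about 5.6 mmHg.

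**Step 5. Sensitivity to treatment (assumed figures, not in the document).** Suppose 12% of exposed and 6% of unexposed participants are on therapy that lowers systolic BP by 10 to 15 mmHg. Unadjusted, this hides 0.06 × 10 = 0.6 to 0.06 × 15 = 0.9 mmHg of the 4 mmHg. In a simulation with treated people drawn from those above the cut-off (903 versus 100, two-sided), power for unadjusted systolic BP falls to about 60% (10 mmHg) or 54% (15 mmHg). Power for hypertension stays near 52%, because treated people count as cases.

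**The case against.** Four points can be made for the plan as written.

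- **The continuous analysis is still there.** A reader might infer that the plan no longer answers Objective 2. The text does not support that: the sentence after the primary-outcome definition plans linear regression on blood pressure as well as logistic regression on hypertension. This stands. The power loss applies only to the outcome that carries the primary label.
- **The fall from 80% is not all due to dichotomising.** A reader might infer that power drops from 80% to about 50%. The figure of about 50% needs a two-sided test at 938 to 1,003 participants. Under that same test, systolic BP itself has only 69–72%. At N=1,003, about 8 of the points between 80% and 52% come from unstated sidedness or sample size.
- **Hypertension has a real advantage.** Counting people on therapy as cases is a legitimate allowance for treatment, and Step 5 shows that it can remove most of the power gap if systolic BP is analysed without adjustment. This stands too. It is a reason to choose hypertension deliberately and say so, but it does not align the objective with the power statement. How treated values enter the linear model is detail that an article may leave to the SAP, so silence on it is not an error here.
- **The 4 mmHg scenario is illustrative and the overall N rests on prevalence.** That is true, and Objective 2 covers many exposures. But the Sample size section claims enough power for the other aims, and for Objective 2 it supports the claim only for systolic BP.

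On confounders, existing literature is named beside univariate results, so screening is not the only criterion. It remains a stated one.

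**Conclusion.** The inconsistency is real and worth correcting. In each variant checked at 30% prevalence, the outcome labelled primary has 50–64% power for the planned 4 mmHg difference, 18 to 20 points below systolic BP under the same test and sample size. It misses the stated 80% every time.

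The figures assume normal systolic BP with equal SD, hypertension defined by a systolic cut-off alone, and no covariate adjustment. They leave out the diastolic and treatment parts of the definition, which would move the exact values. The gap narrows if treated systolic values are used as measured. The conclusion about the label and the missing power figure does not depend on these assumptions.

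The univariate criterion for confounders is a poor rule that the text fixes, so it should be changed. The document gives no basis for putting a size on its effect.

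**What to change.** 1. Name 24-hour mean systolic BP as the primary outcome of Objective 2, with an allowance for participants on anti-hypertensive therapy (method to be set in the SAP) and hypertension as a secondary outcome. Alternatively, if hypertension stays primary, reword Objective 2 and replace the power statement with one for hypertension, or give its detectable effect (an odds ratio of about 1.83 for 80% power at N=1,003 two-sided, under the assumptions above).
2. State whether alpha is one- or two-sided and which N the power statement uses.
3. Choose confounders in advance from subject knowledge, and delete the reference to univariate results from the adjustment rule.

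The cost is wording in the protocol and SAP, plus one model for treated values. Medication use is already part of the baseline assessment, so no new data are needed. The article says the SAP will be produced before data collection is completed, which is the natural place to settle this.

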**Figure 1. f1:**
[figure not shown]
Map showing location of study sites. West Kiang Health and Demographic Surveillance System (The Gambia) and Kilifi Health and Demographic Surveillance System (Kenya). This figure is an original figure produced by the authors for this article.

Kilifi County is one of the poorest regions in Kenya
^
40
^. The Kilifi Health and Demographic Surveillance System (KHDSS), covers an area of 900 km
^2^ and has a population of around 300,000 people. The prevalence of hypertension is 26% and only 3% of individuals have their blood pressure controlled
^
41
^. Further evidence of the consequences of poor hypertension control is the high incidence of cardiovascular disease in the area, with more than one third of patients admitted with cardiovascular disease dying during their hospital stay
^
31
^.

CHWs deliver health services at the community level and work within a Community Health Unit (CHU), a health service delivery structure within a defined geographical area covering approximately 5,000 people (500–1000 households). CHWs are selected from the community they serve and where possible, are required to have completed secondary education. Each CHU is required to have approximately 10 CHWs.

The Kiang West district in The Gambia covers 750km
^2^ and includes 36 villages with a population of over 14,000 individuals. It is one of the poorest regions in the country with all households in the lowest or low wealth groups. Hypertension prevalence in this region is estimated to be 40%, of whom at least 71% are undiagnosed, and only 4% controlled
^
42
^. The health service delivery in the region is coordinated through the Regional Health Team of the Lower River Region (Mansakonko Administrative Area). The community health nurses (CHNs) deliver services in a defined village cluster within the district. There are 4 CHNs in Kiang West with each handling 7–9 villages. CHNs work with and supervise the village health workers (VHW) who are selected by their communities.

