**Figure 2. f2:**
[figure not shown]
Flow diagram showing participant recruitment, study procedures and objectives.

*Inclusion criteria:*

•   Registered in population registers of the KWHDSS (The Gambia) or KHDSS (Kenya)

•   Aged ≥30 years at the time of enrolment in the study

•   Able to provide written informed consent to participate in the study

*Exclusion criteria*

•   Pregnant women (self-reported)

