### Study procedures

**
*Baseline assessments*.** Baseline assessments will collect information including demographics, household assets, anthropometrics, diet, physical activity, history of hypertension and medication use for hypertension and other diseases (
Table 3).

**
*Blood pressure assessment*.** We will conduct a cross-sectional study over two weeks to determine the accuracy of three BP measurement methods compared to the reference standard of 24-hour Ambulatory BP Measurement (24-hr-ABPM). The alternative BP measurement methods are: 1) Attended Automated BP Measurements (aABPM); 2) Unattended Automated BP Measurements (uABPM); and 3) Home-Based BP Measurement (HBPM). Details for all BP measurement methods are summarised in
Table 1 and
Table 3.

All BP measurements will be conducted by CHWs trained by the study team to perform the blood pressure measurements based on study SOPs. The competencies of the CHWs will be assessed by the study team prior to data collection and at regular intervals during data collection. The CHWs will then collect blood pressure measurements in a random order at participants’ homes. The random order of blood pressure measurements for each of the participants will be set using a computer-generated randomisation list produced prior to measurements starting.

Each participant is expected to have completed all four BP measurements over a two-week period. A schematic overview of the procedure is shown in
Figure 3. We will follow relevant international cardiological society guidelines for conducting all BP measurements
^
45–
47
^.

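### The linear models for systolic BP in Objective 2 state no correction for antihypertensive treatment, although the binary outcome does, so positive associations would be biased toward zero if treated values are used as measured

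*Protocol article*

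**What the plan says.** Under Study aim and objectives, Objective 2 of the protocol article is "To determine the relationship between systolic blood pressure and potential risk" factors. The matching paragraph under Sample size is also in systolic BP: 1,003 participants, 10% exposed, a standard deviation of 15 mmHg and a difference of 4 mmHg.

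The risk-factor paragraph under Statistical analysis plans names a binary outcome: "The primary outcome will be hypertension, defined as a BP of >140/90mmHG using 24-hour BP measurement, or ongoing therapy with anti-hypertensives". It then plans to examine the "relationship between the candidate risk factors and blood pressure and hypertension using multivariate linear and logistic regression methods as appropriate". The linear part has no rule for people on treatment: no added constant, no censored model, no exclusion. Covariates are chosen as follows: "We will include confounders in the regression models based on results of univariate models and existing literature on the subject".

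Treated people will be in the sample, because self-reported pregnancy is the only listed exclusion. The baseline assessments record "history of hypertension and medication use for hypertension and other diseases". The treated proportion is not given. Under Study setting, hypertension prevalence is 26% in Kilifi; in Kiang West it is "estimated to be 40%, of whom at least 71% are undiagnosed, and only 4% controlled".

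**The concern.** A treated person's measured systolic BP is the underlying value minus the drug effect. Treatment is given because pressure is high, so the values lowered lie mainly in the upper tail. An exposure that raises systolic BP puts more people into that tail, hence more into treatment, and part of its effect is removed from the measured data.

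The phrase "or ongoing therapy with anti-hypertensives" shows that the authors saw this for the binary outcome. One paragraph thus gives a treatment rule for one of its two outcomes and none for the other, which is the one that Objective 2 and its power statement name. A treated, well-controlled participant would be a case in the logistic model and could enter the linear model with a normal value.

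The stake is larger for exposures linked to contact with care (age, site, household wealth or HIV, for example). Their treatment rates may differ beyond what blood pressure explains.

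The covariate rule does not remove the problem. Treatment may well show a univariate association with systolic BP and so enter as an ordinary covariate. It is a consequence of high pressure, so conditioning on it does not recover the underlying value.

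**Working it through.** **Inputs from the protocol article.** N = 1,003, 10% exposed (100.3 v 902.7), SD 15 mmHg, difference 4 mmHg, alpha 0.05 (sidedness not stated). Prevalence of hypertension 26% (Kilifi) and 40% (Kiang West), with 30% as the planning value. At least 71% undiagnosed in Kiang West, so at most 29% of hypertensives there can be on treatment: 0.40 × 0.29 = 11.6% of adults.

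**Assumptions.** Share q of hypertensives treated: 0.05 to 0.29, with the Kiang West ceiling also applied to Kilifi, for which no such figure is given. Drug effect D: 5 to 20 mmHg. Underlying systolic BP is normal, and hypertensives are its upper tail at prevalence p (diastolic pressure ignored).

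**1. The plan's own figure.** SE = 15 × √(1/100.3 + 1/902.7) = 1.579 mmHg. For 4 mmHg, power is 81.3% one-sided and 71.7% two-sided. The stated 80% is reproduced one-sided only. That is a separate matter, but it shows that there is little slack.

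**2. Equal treatment rates among hypertensives.** Let h1 and h0 be the proportions of exposed and unexposed in the hypertensive tail, with 0.1·h1 + 0.9·h0 = p and means 4 mmHg apart. Then

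observed difference = 4 − D × q × (h1 − h0).

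| p | h1 | h0 | h1 − h0 | q = 0.05, D = 5 | q = 0.29, D = 15 | q = 0.29, D = 20 |
|---|---|---|---|---|---|---|
| 0.26 | 0.343 | 0.251 | 0.092 | 3.98 | 3.60 | 3.47 |
| 0.30 | 0.387 | 0.290 | 0.097 | 3.98 | 3.58 | 3.44 |
| 0.40 | 0.494 | 0.390 | 0.105 | 3.97 | 3.54 | 3.39 |

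Worst cell: 4 − 20 × 0.29 × 0.105 = 3.39 mmHg, a loss of 0.61/4 = 15%. Mildest cell: 3.98 mmHg, a loss of about 1%. With D up to 15 mmHg the loss is at most about 12%, and two-sided power falls from 71.7% to between 61% and 71%.

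**3. Exposure tied to treatment.** Let T be the share of all participants treated and R the ratio of treated shares, exposed to unexposed. Then t0 = T/(0.9 + 0.1R), t1 = R·t0, and observed difference = 4 − D × (t1 − t0).

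- T = 5%, R = 2: 9.1% v 4.5% treated, giving 3.55 mmHg (D = 10) and 3.32 mmHg (D = 15).
- T = 5%, R = 5: 17.9% v 3.6% treated, giving 2.57 mmHg (D = 10) and 1.86 mmHg (D = 15).

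T and R here are assumptions; the documents give neither.

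**4. What a reversal would need.** The sign changes only if t1 − t0 exceeds 4/D: 40 percentage points at D = 10, 27 at D = 15, 20 at D = 20. At D = 15, among ratios of 1, 2, 3 and 5 and treated shares of 3% to 11.6%, this occurred only at R = 5 with T of 10% (35.7% v 7.1%, −0.29 mmHg) or 11.6% (41.4% v 8.3%, −0.97 mmHg). At D = 10 it did not occur.

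**The case against.** The strongest objection is that the article is silent here rather than wrong. It calls its statistical section a summary and promises a detailed statistical analysis plan, which is not at hand. The words about linear and logistic regression as appropriate leave room for a treatment correction, and medication data are collected, so nothing in the design prevents one. That much stands: a reader might infer that treated values will certainly enter as measured, and the text does not say so. The point is therefore conditional. It remains more than missing detail, because the same paragraph writes a treatment rule for one outcome and leaves it off the one that the objective names.

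Second, the named primary outcome is binary and already counts treated people as cases. This also stands, and it confines the point to the linear models.

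Third, the size rests on assumptions. The documents give no treated share and no drug effect; 29% is an upper limit on diagnosis at one site, and not everyone diagnosed is treated. Several candidate factors, such as the protective genotypes and indoor air pollution, have no documented link to treatment, so for them only the small loss in step 2 would be expected. All of this is right and is why ranges are shown. It limits the size and leaves the direction unchanged.

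A reader might also infer that associations could be reversed. Step 4 shows that this needs a treated-share gap for which the documents give no basis.

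**Conclusion.** The point holds in a limited form. The article builds treatment into the binary outcome but states no correction for the linear models of blood pressure that serve Objective 2. If measured systolic BP of treated participants is used unadjusted, positive associations are biased toward zero. The loss is modest for most exposures, about 1 to 15% of a 4 mmHg effect, given equal treatment rates among hypertensives and the assumed ranges for treated share and drug effect. It can be material for exposures strongly tied to contact with care, but how large depends on treatment ratios that the documents do not give. The direction in the equal-rates case needs only that treatment follows high pressure and lowers it. The correction is standard and nearly free, so it should be made.

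**What to change.** State in the analysis plan how treated participants' systolic BP is handled in the linear models, using the medication data from baseline:

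- add a fixed constant to treated participants' systolic BP and show the results at two values, for example 10 and 15 mmHg; or fit censored-normal regression with treated values as right-censored;
- do not simply enter treatment as a covariate, and keep it out of the univariate screen for confounders;
- report the uncorrected model as a sensitivity analysis.

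The logistic analysis of hypertension needs no change on this account. The cost is a few sentences and a few lines of code, with no new data. The downside is that the constant is itself an assumption, which is why two values should be shown.
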